### Loss to follow-up

In accordance with the Russell Standard [20], we will conduct an intention-to-treat analysis, and assume those lost to follow-up are smokers. We will make three attempts to contact participants using their preferred method before an attempt at follow-up is abandoned.

### Trial closure

The end of the trial is defined as the last date of follow-up of the last patient, following database lock. However at present there is uncertainty as to when the last follow-up will take place. We will conduct a futility analysis with the aim of saving the resources of the funding body (NIHR HTA). The futility analysis will take place 30-months post the commencement of recruitment, or as soon thereafter as possible, when all the primary outcome data are collected. The analysis will examine the difference between arms in the frequency of occurrence of the primary outcome (six month follow-up data). If there is a lack of significant effect (*P* <0.05) at six month follow-up, then the 12 month follow-up shall be terminated and the study will close 36 months after commencement. If there is a significant difference in six month abstinence then 12 month follow-up will be completed, taking the study to 42 months duration.

### Statistics and data analysis

#### **
*Sample size*
**

This is determined based on plausible estimates of the six month confirmed prolonged abstinence rate in the control group and the effectiveness of preloading. A recent trial showed a six month abstinence rate of 15% [33]. Another trial of 631 participants also found a similar prolonged abstinence rate [34]. We have therefore settled on an abstinence rate in the control group of 15%. Our meta-analysis found summary RRs of 1.05 for short-term and 1.16 for prolonged abstinence [8]. However, there was heterogeneity, perhaps explained by use or non-use of the patch, but other differences between trials make this uncertain. It is therefore difficult to settle on a specific RR, but we chose 1.4 as plausible and an effect likely to interest the NHS SSS. The RR (95% CI) for abstinence in the patch trials in our review [8], was 1.17 (1.00, 1.37) for short-term and 1.26 (1.03, 1.55) for long-term abstinence, but with unexplained heterogeneity, so our RR appears reasonable. For example, an RR of 1.4 means that the summary effect for NRT is about 2.2, similar to that for varenicline versus placebo (2.3) [3]. This gives us a sample size of 893 participants per arm or 1786 in total for 90% power, calculated with Yates correction using nQuery (Statistical Solutions Ltd, [name]) (Table 2).

**Table 2 T2:** Sample sizes required for different combinations of power and relative control versus intervention six-month abstinence rates

		**Trial with 80% ****power**	**Trial with 90% ****power**
**% prolonged abstinence in control**	**% prolonged abstinence in intervention**	**Number/arm**	**Number/arm**
RR = 1.3			
14	18.2	1249	1655
15	19.5	1150	1524
16	20.8	1064	1409
20	26	805	1065
RR = 1.4			
14	19.6	734	970
15	21	676	893
16	22.4	625	825
20	28	471	622
RR = 1.5			
14	21	490	646
15	22.5	451	594
16	24	416	549
20	30	313	412

The mediation analysis will proceed using the procedure outlined by MacKinnon, using regression modelling [36]. We will estimate the mediated effect using mediation regression equations, modelling the association between abstinence (dependent variable) and intervention, and between abstinence (dependent variable), the intervention and the potential mediators, in both cases using logistic regression. The association between (continuous) mediators and the intervention will also be modelled using linear regression. The mediated effect will be estimated by the product of coefficients method, using the appropriate coefficients from the regression models, and using boot strapping to compute confidence limits of the mediated effect. We also propose a two-step mediation process, whereby preloading leads to higher nicotine concentration (reflected by cotinine concentration), which in turn leads to reduction in measures of dependence that lead to improved abstinence. We will examine this using Mplus (Muthén & Muthén, [name]) with a structural equation model.

We will conduct exploratory subgroup analyses to examine whether the effect of preloading is similar for people who use varenicline or those using NRT (we expect the proportion using bupropion to be small), first testing for effect modification with a multiplicative interaction term in logistic regression. Similarly we will examine whether the effect of preloading is modified by dependence level (assessed by FTND, exhaled CO, and salivary cotinine), demographic characteristics, previous use of pharmacotherapy to quit, and smoking history. We will also investigate the proportions of reactors and non-reactors to the preloading treatment (those who do and/or do not experience reductions in CO, cigarettes per day and cigarette reward, between baseline and the visit one week following this), whether quit rates differ between these two groups, and whether this is modified by the pharmacotherapy participants are provided with from the NHS SSS.

We aim to address two aims concerning weight gain during a cessation attempt, details of the analysis plan for these can be found in Additional file 2.

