We concluded that there was insufficient evidence to recommend preloading as a strategy for use routinely and that further trials were needed to confirm effectiveness. The best supported hypothesis was that preloading may work by altering desire to smoke. The trials were heterogeneous in ways that defied easy explanation. This raises the possibility that there is true heterogeneity in response to preloading with nicotine patches. Some people may benefit and others may not benefit from preloading.

Investigating mediation is important. Variation in response to the mediator is likely to give a much clearer signal about the efficacy of a particular strategy for preloading than is longer-term abstinence, and it has important practical implications for treatment. Instituting preloading in the stop smoking service (SSS) would cost approximately £50 million. If preloading was effective for only half of users, it would be useful to know which half. If we could monitor response to treatment (monitor a mediator), then we might be able to stop preloading in patients who are not responding, saving tens of millions of pounds. Alternatively, we could use the patient’s response measured by the mediator to adjust treatment (such as dose, duration, or form of medication) to enhance efficacy.

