### Assessment and follow-up

#### **
*Assessment*
**

The primary and secondary outcomes will be measured as detailed in the previous ‘Trial design’ section. Further outcomes shall be assessed as follows:

At baseline, the researchers will collect the information stated in Table 1. Educational qualification and occupational classification will be classified in categories used in the UK Census 2011 [24], ethnic group will be classified according to categories used by the NHS SSS, based on the UK Census 2001, and exhaled CO will be measured using a CO monitor, as a measure of smoke intake.

Potential mediators of the preloading effect will be assessed at baseline, one week later during the pre-quit period, one week after quit day, and six and 12 months after quit day.

Dependence will be measured at baseline using the Fagerstrom Test for Nicotine Dependence (FTND) [25]. The FTND will be re-administered at the week following baseline visit, and at six and 12 month follow-ups. However, for the purposes of the analysis we will exclude the cigarettes per day item, which might reasonably be expected to decline in the active patch group without necessarily indicating reduced dependence.

Changes in reward from smoking, measured using the modified Cigarette Evaluation Questionnaire (mCEQ) [26], will be measured at all contacts (at post-quit contacts this will only be in those who have returned to smoking). We will ask the participant to focus on the cigarette after the evening meal (or equivalent in shift workers). For those who smoke after quit day, we hypothesize that preloading may result in decreased reward from smoking. The mCEQ measures satisfaction, taste, mood, cognitive, and sensory sensations to smoking particular cigarettes. At pre-quit contacts we will also use two simple, single item rating scales which provided more useful data than the mCEQ in our trial of varenicline preloading [27]. These ask participants to rate ‘Have you found your urges to smoke stronger or weaker than usual in the last week’ with response options of ‘Much stronger; slightly stronger; same as before; slightly weaker; much weaker’; and ‘Have you found cigarettes more or less enjoyable than usual in the last week?’ with response options of ‘Much more enjoyable; slightly more enjoyable; same as before; slightly less enjoyable; much less enjoyable’. We hypothesize that preloading would reduce satisfaction and the degree to which it does might be associated with improved outcome.

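### The planned mediation model averages the mediator–abstinence slope over both arms, so its product can misstate how a marker relates to quitting on the patch; arm-specific indirect effects should be reported beside it.

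*Protocol article*

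**What the plan says.** The Analysis plan section names three regressions. Abstinence is regressed on the intervention. A second model relates "between abstinence (dependent variable), the intervention and the potential mediators, in both cases using logistic regression". For the mediator itself, "The association between (continuous) mediators and the intervention will also be modelled using linear regression". The mediated effect comes from these: "The mediated effect will be estimated by the product of coefficients method, using the appropriate coefficients from the regression models", with limits obtained by "using boot strapping to compute confidence limits of the mediated effect".

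No arm-by-mediator term is listed, and no check that the slope is the same in both arms. Interaction terms do appear in the same section, but for the exploratory moderator analyses, described as "first testing for effect modification with a multiplicative interaction term in logistic regression".

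Two other places say what the mediators are for. Under Assessment: "We hypothesize that preloading would reduce satisfaction and the degree to which it does might be associated with improved outcome". In the background section on systematic reviews: "If we could monitor response to treatment (monitor a mediator), then we might be able to stop preloading in patients who are not responding".

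One further analysis bears on the point: "We will also investigate the proportions of reactors and non-reactors to the preloading treatment". It classifies people by reductions in CO, cigarettes per day and cigarette reward, and asks whether quit rates differ between the two groups.

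**The concern.** With main effects only, the coefficient b for the mediator is a weighted average of its slopes in the two arms. Multiplying it by the arm effect a answers a question about the patch only if the two slopes agree.

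The intended use makes this matter. Deciding whether a marker's movement during preloading says anything about later quitting needs the marker–abstinence relation among people wearing the patch. A relation found only in controls is carried into the pooled b, multiplied by the patch's effect on the marker, and can appear as mediation. A relation found only on the patch is diluted by the controls. In the first case the trial could point services to a marker that carries no information on the patch. In the second it could undersell one that does.

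**Working it through.** **Inputs from the article.** 893 per arm, 1:1 allocation, control abstinence 15%, risk ratio 1.4 (so 21% on preloading), significance level 0.05, taken as two-sided.

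**The plan's own figure first.** With d = 0.06 and mean proportion 0.18:

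- n = [1.960·√(2·0.18·0.82) + 1.2816·√(0.15·0.85 + 0.21·0.79)]² / 0.06² = (1.0649 + 0.6942)² / 0.0036 ≈ 859.5, so 860 without correction.
- Yates correction: (859.5/4)·[1 + √(1 + 4/(859.5·0.06))]² ≈ 892.5, so 893. This matches the article. It gives no figure for the mediation analysis.

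**Assumptions, because the article gives no values.** Mediator SD 1. The patch shifts it by a = 0.2, 0.3 or 0.5 SD. Slopes are log odds ratios per SD. Limits for the product came from Monte Carlo draws standing in for the bootstrap.

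**Why the pooled slope lands where it does.** Each arm's weight is roughly proportional to p(1−p): control 0.15·0.85 = 0.1275, patch 0.21·0.79 = 0.1659. The shares are 0.1275/0.2934 = 0.435 and 0.565, so b(pooled) ≈ 0.435·b(control) + 0.565·b(patch). With a = 0.5:

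- Control 0.4, patch 0: b ≈ 0.174, product ≈ 0.087; patch-arm truth 0.
- Control 0, patch 0.4: b ≈ 0.226, product ≈ 0.113; truth 0.20.
- Control 0.4, patch 0.3: b ≈ 0.344 against 0.30, about 14% too large.
- Control 0.2, patch 0.3: b ≈ 0.257 against 0.30, about 14% too small.
- Control 0.4, patch 0.2: b ≈ 0.287 against 0.20, about 40% too large.

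Simulation agrees: 0.112 against 0.20 in the second case, 0.171 against 0.150 in the third and 0.129 against 0.150 in the fourth.

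**Marker related to quitting only in controls: how often the 95% interval excludes zero.** Ranges are over the three shifts; the 0.4 row is at a shift of 0.5 SD.

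| Control slope | Planned product |
|---|---|
| 0.2 | 26–31% |
| 0.3 | 55–58% |
| 0.4 | 78% |
| 0.5 | 92–93% |
| 0.7 | about 99% or more |

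With the interaction term, the patch-arm product excludes zero in only about 4–6% of trials.

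**Marker related to quitting only on the patch.** The pooled slope is 0.54–0.58 of the true patch slope (0.47–0.49 if both arms quit at the same rate). Detection is 41–45% for the planned product against 65–70% for the patch-arm product at slope 0.2, and 76–78% against 94–96% at 0.3.

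**Equal slopes, shift 0.5 SD.** Going from the pooled to the patch-arm product, detection falls from about 91% to 69% at slope 0.2 and from over 99% to 95% at 0.3.

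**Interaction test.** Power is about 35% at a slope difference of 0.2, 66% at 0.3 and 97% at 0.5.

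**The case against.** **The article is a summary.** It cites a methods text for the procedure, and neither that text nor a full analysis plan is at hand; either may call for the term. That stands as a caution. But the article does list its equations, and the same section names an interaction term where one is wanted, so the model as stated has main effects only.

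**Nothing in the article predicts unequal slopes.** This is largely right. Its account of mechanism, with lower urges and less satisfaction leading to cessation, fits a common slope. It does accept that a marker may move on the patch without its usual meaning: it drops the cigarettes-per-day item from the dependence score in analysis for that reason. That makes unequal slopes plausible without establishing them.

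**The reactor analysis already looks at response under preloading.** It does, for CO, cigarettes per day and reward, and reward is the construct in the satisfaction hypothesis. It sits outside the mediation model and does not cover urges, stereotypy, aversion, dependence, confidence or motivation.

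**A control-only marker is not a false pathway in every sense.** Evaluated with arm set to control, its indirect effect is genuine (0.8 to 3.4 percentage points in the settings tried). The error concerns the effect evaluated on the patch.

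**The remedy has a price.** If slopes are equal, relying on the patch-arm product gives up roughly half the information on b. This stands, and it is why the pooled product should be kept.

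**The analysis is secondary.** The Discussion says so for all additional outcomes, and the article sets no rule for declaring a pathway.

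**Conclusion.** The point holds as a limited but worthwhile improvement to a secondary analysis. The stated model imposes one slope on both arms. At the planned size, a marker unrelated to quitting on the patch can show apparent mediation in about 30% (control slope 0.2) to 78% (0.4) of trials, and a patch-only marker keeps about 55% of its true mediated effect. Partial differences give errors of about 14% to 40% in the cases tried. All of this rests on assumed slopes and shifts; the extreme cases set one arm's slope to exactly zero.

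A reader might infer that the plan will declare any control-only marker a pathway of preloading, or that the pooled product is invalid and must be replaced. The documents support neither. Apparent mediation needs a real arm shift and a sizeable control slope, no declaration rule exists, and the pooled product is the more precise estimate when slopes agree. What remains is that the monitoring use described in the background depends on the patch-arm relation, and the listed mediation equations do not estimate it.

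**What to change.** In the Analysis plan section:

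1. Keep the pooled product as planned.
2. Also fit each abstinence model with an arm-by-mediator term, and report the indirect effect at each arm level with bootstrap limits: a × b for control and a × (b + interaction) for the patch.
3. Report both whatever the interaction test shows, since its power is only about 35–66% at slope differences of 0.2–0.3.
4. State that any conclusion about monitoring a marker during preloading will rest on the patch-arm estimate.

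The cost is a few lines of wording and one extra term per model, with no new data. The patch-arm estimate will have wider limits than the pooled product when slopes are equal, so the two should be presented side by side.

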### Cost-effectiveness analysis

Cost-effectiveness analysis will be conducted by combining data collected within the trial and existing models. We will calculate the proportion of prolonged abstinent participants produced by the intervention. We will estimate the costs of the behavioral support and NRT using a similar approach adopted in our previous HTA reports and economic modelling [37,38], using local costings where appropriate. These models will enable the calculation of the proportion of lifetime quitters, the cost/lifetime quitter, the cost/life year gained and the cost/quality adjusted life year. We will compare the health service use for the active and control groups to assess whether preloading leads to extra health service use. Longer term NHS costs can be estimated using a cost model recently developed by the Public Health Research Consortium (PHRC), involving one of the investigators [39]. Cost effectiveness acceptability curves will be used to demonstrate the value for money based on a range of threshold values for a quality-adjusted life year (QALY).

### Data handling, record keeping, and retention

The secure online database used for trial identification number allocation and randomization will incorporate an online CRF. There will however also be a paper copy of each CRF (the source documents for the trial). This is because the CRF will need to be completed to correspond with each clinic visit and follow-up; however there may not always be access to a computer or internet connection when trial clinics are taking place. In this case the paper CRF will be completed and data will be copied to the online version at a later date. CRFs will be kept in a locked cabinet in a secure office and department. These will be transferred from the site of the research visits to the universities personally by the researchers, and consent will explicitly be sought from participants to do so. The trial database will be securely developed, held and maintained by the Primary Care Clinical Research and Trials Unit (PC-CRTU) at the University of Birmingham. On completion of the trial and data checking, the CRFs will be transferred to a secure, GCP compliant, external archiving facility, where they will be held for 15 years and then destroyed. The database will be anonymized and a secure compact disc containing the link between identification number and patient identifiable information will be stored in a secure archiving facility.

The trial is being run as part of the portfolio of trials in the Primary Care Clinical Trials Unit (PC-CTU), a National Institute for Health Research (NIHR) recognized trials unit in Primary Care Health Sciences, at the University of Oxford. The data management will be run in accord with the standard operating procedures, which are fully compliant with the Data Protection Act and GCP.

Patient identifiable data will be shared only within the clinical team, on a need-to-know basis, to provide clinical care and ensure good and appropriate follow up. Patient identifiable data may also be shared with participants’ GPs and approved auditors from the REC, NHS Research and Development, or the MHRA. Otherwise, confidentiality will be maintained and no one outside the trial team will have access to either the CRFs or the database.

### Safety monitoring plan

#### **
*Risk assessment*
**

A risk assessment has been carried out in accordance with MHRA guidance on Risk Adapted Approaches to Monitoring. A suitable monitoring plan will be drawn up and appropriate on-site and central monitoring will be performed.

### Monitoring at the study coordination centre

The trial will be conducted in accordance with the risk assessment, monitoring plan, current approved protocol, GCP, relevant regulations, and standard operating procedures.

Monitoring will be performed by the University of Oxford’s Clinical Trials and Research Governance (CTRG) Office according to CTRG standard operating procedures and GCP. Data will be evaluated for compliance with the protocol and accuracy in relation to source documents. Following written standard operating procedures, the monitors will verify that the clinical trial is conducted and data are generated, documented, and reported in compliance with the protocol, GCP, and the applicable regulatory requirements.

Data cleaning will take place by a series of logical checks on the electronic data (for example, a person cannot be recorded as a prolonged abstinent smoker at six months if they were not in such a state at four weeks). Discrepant records will be checked with the source documents and the database amended if necessary.

The trial may be subject to monitoring by the lead Comprehensive Local Research Network (CLRN). Direct access will be granted to authorized representatives from the Sponsor, host institution, and the regulatory authorities to permit trial-related monitoring, audits, and inspections. Therefore, participants will be asked for consent to allow their records to be viewed by these authorities.

### Monitoring at local sites

The monitor will perform site visits. The team will be trained in all aspects of the protocol and trial procedures, and the monitor will check this as a part of their visit (compliance to protocol, delegation logs and curriculum vitae).

### Serious breaches

The Medicines for Human Use (Clinical Trials) Regulations contain a requirement for the notification of ‘serious breaches’ to the MHRA within seven days of the Sponsor becoming aware of the breach.

A serious breach is defined as ‘a breach of GCP or the trial protocol which is likely to affect to a significant degree:

a) the safety or physical or mental integrity of the subjects of the trial; or

b) the scientific value of the trial’.

In the event that a serious breach is suspected the Sponsor must be contacted within one working day. In collaboration with the CI, the serious breach will be reviewed by the Sponsor and, if appropriate, the Sponsor will report it to the REC, MHRA, and the NHS host organization within seven calendar days.

